### Variables and Outcomes

#### Implementation

The implementation outcomes of this study include both process and intervention-related measures. The implementation process will be analyzed using the CFIR, focusing on outer setting, inner setting, and individual characteristics. The outer setting includes external influences such as patient needs, resources, and organizational networks. KBs recruited from each setting will undergo an initial assessment to identify key considerations, constraints to sustaining the KB role beyond the study, and an intake analysis of individual actions. These factors will be examined in initial KB analyses, monthly KB meetings, and a post hoc multisite analysis. Additionally, external factors such as cosmopolitanism (organizational networking), peer pressure, and policies or incentives supporting leisure-related outcomes will be assessed to determine their role in technology adoption and resource integration. The inner setting includes organizational characteristics affecting implementation, including team culture, intervention compatibility, goal-setting structures, leadership engagement, and implementation climate, which will be analyzed qualitatively through meeting minutes from monthly KB sessions. Individual characteristics, including KBs’ beliefs, knowledge, self-efficacy, and personal attributes influencing implementation, will be assessed during onboarding interviews with the research coordinator. User characteristics (eg, disability type, age, socioeconomic status, language, and technology familiarity) will be analyzed preimplementation during user-centered design activities and pilot testing. These insights will inform KBs’ strategies and interventions.

The implementation and intervention outcomes will assess the expansion of KB networks using social network analysis, as well as the growth in Jooay App users and their engagement levels. Additionally, partners with lived and living experiences (PWLEs) identified increased community awareness of leisure activities as a key implementation outcome, emphasizing its significance in post-COVID public policy and service restructuring. This outcome will be measured through quantitative indicators, including social network analysis and the number of new organizations and activities added to the app during the intervention period, compared with previous registration cycles.

#### Effectiveness

##### Individual Level

###### Feasibility Outcomes

Feasibility will be assessed based on several key indicators: enrollment rate, completeness of data collection, participant retention, and level of technical assistance required. Factors that contribute to the feasibility of using a mobile app in everyday life will also be explored through exit interviews with participants.

###### Engagement

The objective user engagement will be assessed through app analytics data, including interactions with gamification features. This data will provide insights into the frequency of app access as well as engagement with specific gamification elements throughout the study period.

###### Acceptability

The subjective user engagement will be assessed using the System Usability Scale (SUS) [26]. The perceived quality of the Jooay App and impact on the knowledge, attitudes, intentions to participate in leisure activities, and the likelihood of actual change in the target health behavior will be evaluated using a modified version of the Mobile App Rating Scale (MARS) [27].

###### Participation

Participation’s attendance and involvement will be assessed using the “Activity Planner” and “My Summary” features within the Jooay App. The “Activity Planner,” a gamification feature, will allow users to track their planned leisure activities and monitor their completion rates. This feature provided insights into users’ engagement in planned leisure activities over the course of the study. The “My Summary” feature stored users’ responses to self-assessment questionnaires, in which they reflected on their experiences after participating in a specific leisure activity. Users expressed their feelings about the activity by selecting an emoji and identified the benefits gained by choosing relevant domains from the F-word framework for childhood development [28].

### Community Level

The effectiveness of the gamification-based mobile app intervention will be assessed primarily through user engagement metrics collected through app analytics, including the number of clicks, logins, active time spent, access frequency of individual gamification features, comments, and reviews. These data will provide insights into how youth, caregivers, and professionals interact with the app over time. Additionally, differential outcomes will be examined for health care and education professionals, focusing on the integration of community participation into intervention plans and health promotion strategies. For youth, the impact of the intervention will be evaluated based on increased participation in community activities, collected from the “Activity Planner” and “My Summary” features within the Jooay App.

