**Methods:**

A hybrid type II effectiveness-implementation study will be conducted. The Consolidated Framework for Implementation Research (CFIR) will guide implementation strategies, including the expansion of knowledge broker (KB) networks to raise the profile of adaptive and inclusive leisure activities in Canada. An interrupted time series (ITS) design will be used to evaluate implementation outcomes across 5 provinces in Canada. Process evaluation will analyze inner and outer setting characteristics, KB strategies, and community resource mobilization. Effectiveness outcomes will be assessed through two phases: (1) a nonrandomized mixed methods pilot feasibility study of the app, where acceptability, engagement, implementation, and potential benefits will be measured, and (2) an ITS at the population level, where overall app usage (eg, clicks, logins, and time spent), individual gamification feature metrics, and user feedback will assess effectiveness outcomes.

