### Objectives

The primary objective of this study is to evaluate whether the deployment of the gamified version of the Jooay App is associated with changes in app engagement compared with the previous nongamified version. Specifically, we will examine changes in app engagement following the deployment of the gamified Jooay App, using an interrupted time series (ITS) analysis of aggregated app analytics data.

The secondary effectiveness and feasibility objectives are to examine changes in specific engagement indicators, including app sessions, active users, duration of use, frequency of use, and use of key app features; to evaluate the feasibility of the gamified Jooay App among youth with disabilities, parents, and clinicians; and to explore postdeployment participation-related outcomes, including planned activities, attended activities, satisfaction, and perceived achievement.

The implementation objectives are to assess the process of implementing and scaling up the gamified Jooay App across participating Canadian provinces; to describe the expansion, role, and activities of the Jooay KB networks across these provinces; to identify provincial barriers and facilitators influencing app uptake, implementation, and sustainability; and to examine how the app and KB networks support the identification of community-based play and leisure opportunities for children and youth with disabilities.

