
#### Effectiveness

After signing the consent, during the preparation phase for the pilot study, each participant will receive a tutorial guide for the Jooay App test version. This guide will include instructions on how to navigate and use the app’s various features. Following this, the primary author (EM) will meet individually with each participant, either in person or through an online video call, for an onboarding meeting. During this meeting, participants will be guided through the process of downloading and installing the app on their device, ensuring they feel comfortable with the setup and settings. Participants will have the opportunity to ask any initial questions or concerns regarding the app or study procedures. During the study period, participants will be encouraged to use the Jooay App regularly, engaging with its gamification features to support their participation in leisure activities and work toward their set goals. The research team will be available to answer questions, resolve technical issues, and provide additional guidance as needed. Participants will have direct access to the researcher via email and phone, allowing them to reach out at any time for assistance or clarification. Participants will agree on the periodicity and format of reminders they want to receive to use and engage with the app (eg, weekly, biweekly, monthly email reminders, text messages, or no reminders). The prompts and reminders will be registered in a participant’s “journal” for reference on the types of reminders that might contribute to higher or lower engagement. The preferred frequency and modes will be integrated into the broad public test version as in-app push notifications, email, or text reminders for users. At the end of the study, participants will complete an online survey on Microsoft Form (Multimedia Appendix 1) to capture their overall experiences and perceptions of the Jooay App, covering aspects such as user engagement, satisfaction with specific app features, and any perceived impact on their participation in leisure activities. Participants will be invited to individual semistructured interviews (Multimedia Appendix 2 for interview guide) via Teams to provide clarification and depth to their answers and experiences.

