##### Community Level

Engagement will be measured using a segmented linear regression model to analyze changes over time, including preintervention trends, immediate changes before and after the intervention, and postintervention trends. Where appropriate, models will account for autocorrelation, seasonality, and nonindependence of repeated observations over time. App usage data will capture time spent and interactions with gamification features, with descriptive statistics assessing usage patterns by province, disability, and age among youth participants. Outcomes available only in the gamified version, including planned and attended activities, satisfaction, and perceived achievement, will be analyzed descriptively and longitudinally during the postintervention period rather than included in the primary ITS comparison.

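### No single primary engagement metric is fixed that means the same thing before and after deployment, and the sections that define the primary comparison disagree

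*Protocol article*

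**What the plan says.** The primary objective (Objectives) asks whether deployment is "associated with changes in app engagement compared with the previous nongamified version". It does not say which measure of engagement is meant. The next paragraph of Objectives sets as secondary aims to "examine changes in specific engagement indicators, including app sessions, active users, duration of use, frequency of use, and use of key app features".

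Under Variables and Outcomes, the Community Level section says that effectiveness "will be assessed primarily through user engagement metrics collected through app analytics", and gives as examples "number of clicks, logins, active time spent, access frequency of individual gamification features, comments, and reviews". The abstract (Methods) describes the second effectiveness phase as "an ITS at the population level, where overall app usage (eg, clicks, logins, and time spent), individual gamification feature metrics, and user feedback".

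Under Analysis, Effectiveness, the Community Level section sets a rule that points the other way: "Outcomes available only in the gamified version, including planned and attended activities, satisfaction, and perceived achievement, will be analyzed descriptively and longitudinally" after deployment, and they stay out of the primary ITS comparison.

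Two further passages matter. The Participation section describes the new features: an Activity Planner, and a self-assessment in which the user picks an emoji and benefit domains. The Effectiveness part of Procedures says that the reminder modes preferred in the pilot will be "integrated into the broad public test version as in-app push notifications, email, or text reminders for users".

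**The concern.** A before-after comparison needs an outcome that is measured the same way on both sides of the interruption. Three things stand in the way.

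- **No metric is chosen.** Six are named as the main basis and none is designated. Some reappear in Objectives as secondary under slightly different names.
- **One metric has no pre-deployment values.** The preintervention segment consists of the nongamified version, so access to gamification features is zero there by construction.
- **Two metrics change content at deployment.** Clicks and active time are logged in both versions, but planner entries, emoji ratings and domain choices add taps and minutes that the old version could not generate. No section says whether activity on the new screens counts in the comparison.

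At stake is what the headline result means. A rise in clicks or time could show that the app has more to tap, and not that people use it more. If the metric is chosen after the series has been seen, the primary comparison is hard to defend.

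**Working it through.** The article gives no alpha, effect size, variance or power for the ITS, so there is no figure of its own to reproduce. The check sets the sections side by side and then illustrates the size of the measurement problem under stated assumptions.

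**1. Status of each kind of metric**

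| Metric | Variables and Outcomes, Community Level | Objectives | Before deployment? |
|---|---|---|---|
| Active time / duration of use | main basis | secondary | yes, but content changes |
| Logins / frequency of use | main basis | secondary | yes |
| Access to gamification features / use of key features | main basis (abstract: under the ITS) | secondary | gamification features: no |
| Clicks | main basis | not named | yes, but content changes |
| Comments, reviews | main basis | not named | not stated |

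The analysis section's exclusion rule names planned and attended activities, satisfaction and perceived achievement. These are introduced as examples, so the general wording also covers feature access. It does not reach clicks or active time, which exist in both versions.

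**2. A metric that is zero before deployment**

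Segmented regression with intercept, trend, level change and slope change was simulated on 12 + 12 monthly points (the minimum in Sample Size). It used independent errors, a two-sided 5% t test on the level change with 24 − 4 = 20 degrees of freedom, and 20,000 runs. A series that is zero before and positive after gives a significant positive level change in 100% of runs at a month-to-month coefficient of variation (CV) of 10% or 20%, and in 91% at 50%.

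**3. A metric present in both versions, underlying use unchanged**

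In this design the standard error of the level change is 0.821 × the residual SD. Suppose new screens add a fixed share of logged activity. With +20% and a CV of 10%, the level change is 0.20 / (0.821 × 0.10) = 2.44 standard errors, against a critical value of 2.09. With +10% and a CV of 20%, it is 0.10 / (0.821 × 0.20) = 0.61. Simulated chance of a significant positive level change:

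| Added activity (assumed) | CV 5% | CV 10% | CV 20% |
|---|---|---|---|
| none | 2.4% | 2.6% | 2.4% |
| +10% | 64% | 22% | 8% |
| +20% | >99% | 64% | 21% |
| +30% | 100% | 94% | 41% |
| +50% | 100% | >99% | 83% |

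Neither the added share nor the CV is in the article. The table shows sensitivity and is not an estimate.

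**4. Multiplicity, illustration only**

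Assume 5% per test, independent tests, and that any one positive test counts as success. Six metrics with two coefficients each (level, trend) give 1 − 0.95^12 = 46%. Without feature access, 1 − 0.95^10 = 40%. If all metrics moved together, two independent coefficients would give 1 − 0.95^2 = 10%. The article states neither the alpha nor the success rule.

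**The case against.** The strongest reply is that the analysis section already deals with the structurally zero metric. Its rule is general, feature access falls under it, and its preceding sentence pairs interactions with gamification features with descriptive statistics. The outcomes section does not mention the ITS, and its primarily may mean no more than mainly. This largely stands: feature access should not drive the primary result. What remains is that the abstract puts it under the ITS and the outcomes section lists it without qualification, so the text needs aligning.

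A second reply is that planner use and reminder-prompted visits are engagement with the deployed version, and hence part of the intervention's effect. This also stands in part. Reminders that raise logins, or knowledge-broker training that encourages reviews, are component or co-intervention effects and not measurement error. Removing new-screen events or notification-opened sessions answers a narrower question and belongs in a sensitivity analysis. The reply does not rescue total clicks or minutes as a sole primary measure, because a rise there cannot separate more use from a larger interface.

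A third reply is that an article may leave event definitions and multiplicity handling to a fuller document. That is fair for those details. It does not cover the disagreement within the article over which engagement measures are primary.

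A reader might go further and infer that a positive primary result is largely built in, or that a change in any one of the six counts as success. The documents support neither. Logins, comments and reviews are not inflated by extra screens in the same direct way, the size of any inflation in clicks and time is unknown, and no success rule is stated.

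**Conclusion.** The point holds in a limited form. The article does not fix one primary engagement metric that is comparable across versions, and its abstract, Objectives, outcomes section and analysis section give different accounts of what is primary and what enters the ITS. For clicks and active time, a rise without more underlying use is possible, and the direction of the artefact is upward. Its consequence cannot be sized from the documents: with 10–50% added activity and a monthly CV of 5–20%, both assumed, the chance of a spurious positive level change is anywhere from about 8% to 100%. Those figures also assume independent monthly errors and a 5% two-sided test. The multiplicity figures are illustrative only. The matter should be settled before the ITS begins, and the Results section says that it has not yet begun.

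**What to change.** - Name one primary ITS metric that is defined identically in both versions and recorded in the legacy analytics, for example monthly active users or app sessions. Both are now in the secondary list in Objectives, so the chosen one must be moved up.
- Name one primary effect, for example the modelled difference from the projected baseline averaged over the 12 post-deployment months.
- Make the remaining engagement metrics secondary, using the same names in Objectives and in the Community Level outcomes.
- In the abstract and the Community Level outcomes, list access to gamification features with the descriptive, post-deployment outcomes, and name it in the analysis section's exclusion rule.
- Where event tagging allows, add two sensitivity analyses: clicks and time limited to functions common to both versions, and sessions not opened from a notification.

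The cost is wording plus a check of what the legacy analytics recorded. The sensitivity analyses depend on tagging by screen and by notification, which the article does not confirm. The downside is that fewer metrics can support the headline.

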Following the completion of the pilot feasibility study, the gamified version of the app will be deployed to all users at the community level. The date of deployment of the gamified version will serve as the intervention point for an ITS analysis. This design was selected because gamification will be introduced at the app or community level and cannot be randomized across users once it is deployed. The ITS design will allow us to examine whether the introduction of the gamified version is associated with changes in the level and/or trend of engagement outcomes compared with patterns observed during use of the previous nongamified version. Engagement data will be extracted from in-app analytics and aggregated at monthly intervals. The preintervention segment will include monthly data from the previous nongamified version of Jooay, and the postintervention segment will include monthly data after deployment of the gamified version. We will include a minimum of 12 monthly time points before and 12 monthly time points after deployment to allow the estimation of baseline trends, postintervention changes, and seasonal patterns. Seasonality will be assessed through visual inspection of monthly trends. If seasonal patterns are identified, models will include calendar month indicators. We will also document other major app updates, holidays, school calendar periods, or external events that may influence engagement and consider these in adjusted or sensitivity analyses. Engagement outcomes will be measured using both backend and frontend indicators. Backend engagement measures will include app usage frequency, number of accesses, duration of use, and feature usage as captured through in-app analytics. Frontend engagement measures will include engagement with community-based features for youth users and the inclusion of community play and leisure activities within intervention plans developed by clinicians and educators. Additionally, following the deployment of the gamified version, participation in leisure will be assessed using newly co-designed in-app features that capture the number of activities users plan and attend, as well as users’ self-reported satisfaction and perceived achievement. These outcomes will be examined descriptively and longitudinally during the postintervention period to explore patterns of participation over time and their association with app engagement.

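### Youth impact is to be judged on increased participation that is recorded only after deployment, and the planned association of participation with app engagement is partly built in

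*Protocol article*

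**What the plan says.** The protocol article describes community-level participation in two different ways.

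- **As an impact outcome.** Variables and Outcomes, Community Level, says that for youth "the impact of the intervention will be evaluated based on increased participation in community activities", with the data "collected from the “Activity Planner” and “My Summary” features within the Jooay App". Sampling, Effectiveness, speaks in the same vein of evaluating the app's effectiveness on participation as well as on engagement.
- **As a description after deployment.** The Objectives say only "to explore postdeployment participation-related outcomes, including planned activities, attended activities, satisfaction, and perceived achievement". Procedures, Effectiveness, says that "following the deployment of the gamified version, participation in leisure will be assessed using newly co-designed in-app features". Analysis, Community Level, refers to "Outcomes available only in the gamified version, including planned and attended activities, satisfaction, and perceived achievement" and says that they "will be analyzed descriptively and longitudinally during the postintervention period rather than included in the primary ITS comparison".

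Procedures, Effectiveness, also gives the purpose of the post-deployment analysis: to "explore patterns of participation over time and their association with app engagement".

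Two definitions bear on that association. The individual-level Participation section classes the Activity Planner as a gamification feature. Variables and Outcomes, Community Level, counts clicks, logins, time in the app and use of each gamification feature as engagement.

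**The concern.** Increased participation as an impact criterion needs something to compare with. The features that measure participation arrive with the intervention itself, so the plan supplies neither an earlier value nor a parallel group. A reader of the outcome section would expect an effect on participation that the analysis section cannot deliver.

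The association has a separate problem. Recording an activity is a use of the app, so the same action can enter both variables. A positive association would then appear even if engagement had nothing to do with how often young people take part in leisure.

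Promoting leisure participation is the stated aim of the app, so these are the results that readers will look for. The limitations under Methodological Considerations mention neither the missing baseline nor the overlap.

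**Working it through.** The protocol gives no figure for this outcome, so there is none to reproduce. The check has three steps. The rates in steps 2 and 3 are assumptions and do not come from the protocol.

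**Step 1. What can be estimated.** For engagement, Sample Size sets at least 12 monthly points before and 12 after deployment. For participation, the measure starts at deployment, so there are 0 points before. A segmented regression estimates a change in level or trend against the pre-deployment segment; with no such segment, neither change is defined. No comparison group and no community-level participation measure outside the app is named.

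The protocol itself supplies other reasons why recorded participation could rise after deployment:

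- knowledge brokers promote the app;
- reminders in the form preferred by pilot participants are to be built into the public version, which could raise logging;
- seasonal patterns are treated as possible.

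**Step 2. How far recorded participation can move with no true change.** Recorded activities per user = share logged × true activities per user.

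- With 2 true activities per user per month, and the share of active users who log rising from 10% to 30%: 0.10 × 2 = 0.2 rises to 0.30 × 2 = 0.6.
- With 4 true activities per user per month, and the logged share of activities rising from 0.2 to 0.6: 0.2 × 4 = 0.8 rises to 0.6 × 4 = 2.4.

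Both are threefold rises with flat attendance. They show what the data could not rule out; they are not forecasts.

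**Step 3. The overlap in the association.** Let true attendance per user-month be Poisson with mean 4. Let other app sessions O be Poisson with mean m, independent of attendance, so that the true correlation is 0. Each attended activity is logged with probability q, giving L logged activities. Suppose each log counts as one session, so engagement is E = O + L. Then Cov(L, E) = Var(L) = 4q and Var(E) = 4q + m, which gives

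corr(L, E) = √(4q / (4q + m)).

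| m (other sessions per month) | q = 0.3 | q = 0.6 | q = 1.0 |
|---|---|---|---|
| 2 | 0.61 | 0.74 | 0.82 |
| 6 | 0.41 | 0.53 | 0.63 |
| 12 | 0.30 | 0.41 | 0.50 |
| 30 | 0.20 | 0.27 | 0.34 |

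For example, m = 6 and q = 0.6 gives √(2.4 / 8.4) = 0.53. A simulation of 400,000 user-months agreed with the formula.

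Removing logging sessions from engagement takes away this part-whole overlap but not all of the bias. In a second simulation, a user's general propensity to use the app raised both other sessions (mean 6) and the probability of logging, while true attendance stayed independent of it. With the propensity's standard deviation at 0.5, 1.0 and 1.5, the correlation of logged activities with non-logging sessions was 0.233, 0.349 and 0.245.

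**The case against.** The strongest reply is that the protocol already treats participation correctly where it matters. The Objectives use exploratory language, Procedures and Analysis restrict these outcomes to post-deployment description, and Analysis excludes them from the primary comparison. No pre-post test of participation is planned anywhere. This stands, and it limits the severity. It does not remove the contradiction: the outcome section still sets a criterion that the analysis section cannot meet, and the sampling section repeats the claim.

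A second reply is that the overlap depends on details that the article does not give: which engagement metric enters the association, whether the unit is the user or the month, and how sessions are counted. Several activities could be logged in one session, or in a session opened for another reason, so one session per log is only a modelling convenience. This also stands, and it is why the size is unknown. Overlap in use of the two features themselves remains under any of these choices, unless their events are removed.

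A reader might infer more than the documents support:

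- *That a post-deployment rise would merely show uptake of the logging tool.* It might also reflect real change, user growth, season or broker activity. The design cannot tell these apart.
- *That users who attend but do not log are counted as non-participants.* The protocol gives no denominator and no rule for users who do not log.
- *That the whole association would be an artefact.* Only part of it is built in, and a true link may exist as well.

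**Conclusion.** Wrong as written, of moderate severity. The impact wording for youth participation conflicts with the protocol's own statement that these outcomes exist only after deployment and will be described. With zero pre-deployment months and no comparator, no effect on participation can be estimated. This conclusion rests on the text alone.

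The planned association with engagement is partly built in because use of the two features counts on both sides. The correlations of 0.20 to 0.82 rest wholly on the assumed rates in the working, so they show that the overlap can matter, not how large it will be.

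It would be tempting to conclude that the effectiveness evaluation as a whole is invalid. The documents do not support that: the primary objective concerns engagement, participation is secondary and exploratory, and the primary interrupted time series does not use it.

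**What to change.** 1. In Variables and Outcomes, Community Level, and in Sampling, Effectiveness, replace the impact and effectiveness wording for participation. State that recorded participation will be described after deployment and that no effect on participation will be claimed, in line with Objectives, Procedures and Analysis.
2. Report two quantities separately by month: the share of active users who log, and the activities recorded per logging user. A change in logging uptake can then be seen beside the recorded activity.
3. For the association, compute engagement without Activity Planner and My Summary events. Label the result exploratory, and say that more engaged users may still log more completely, which the exclusion does not correct.

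The cost is small. The ITS study and its analysis had not begun at submission, items 1 and 2 need wording and simple tabulation, and item 3 needs an event filter. The filter must be applied at extraction, because the analytics are to be aggregated monthly and analysed in aggregate form. The downside is that the participation claim becomes purely descriptive.
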